## Abstract

**Background:**

Treatment of headache disorders is not always optimal. Patients are treated in multiple ways, and the lack of scientific arguments for referral and the insufficient implementation of guidelines result in unclear treatment strategies.

The coexistence of headache and neck pain can lead to the referral to a musculoskeletal physiotherapist. This treatment can only be successful if an underlying cervical segmental dysfunction is present. In such cases a physical treatment can be a valuable option that should be considered.

The aim of this study is to identify prognostic therapeutic patient characteristics and to increase the number of correct physiotherapy referrals.

**Methods/design:**

This trial is designed to identify patient characteristics which can influence the prognosis of the patient. Patients with recurrent headache and co-existent neck pain are recruited via a multicenter setup. After screening for eligibility, subjects are tested at baseline and randomly allocated to one of two treatment groups. Testing includes the administering of questionnaires (a Headache Diagnosis Questionnaire, Headache Inventory List and the Headache Impact Test (HIT-6)) and physical tests (Thermal Stimuli, Manual Cervical Spine Examination and Pressure Algometry). Treatment groups are a usual care group (UC) administered by the General Practitioner (GP) and a usual care plus musculoskeletal physiotherapy treatment group (UCMT). UC is based on the Dutch GP Guideline for Headache. UCMT consists of the UC plus a combination of exercises and spinal cervical mobilisations. Follow-up measurements consist of the completion of the Headache Inventory List, the HIT-6 and scoring of the global perceived effect (GPE). The latter allowing the distinction between responders (positive effect) and non-responders (no effect or worse). Logistic regression analysis will be used to identify the specific patient characteristics of the responders and the non-responders. The additional value of the musculoskeletal physiotherapy will be examined. Follow-up measurements up to 52 weeks are scheduled.

**Discussion:**

This trial aims to identify prognostic patient characteristics, in order to supply a useful diagnostic tool for all health care workers, dealing with headache sufferers.

## Background

Headache is a common disorder with a high impact, both on the socio-economic level and on the level of the individual sufferer [1-3]. Not all headache patients seek headache treatment, although severe pain and disability have been reported even in large proportions of non-care seekers [4]. Patients do not look for treatment partially out of ignorance of effective treatments or because of previous negative experiences [2,5].

Guidelines for headache management in primary care are available [6,7]. These guidelines provide diagnostic and therapeutic algorithms and stepped treatment plans for the most common headache types. Apparently they are insufficiently applied in daily practice as patients are frequently referred to neurology clinics after no more than one visit to the general practitioners (GP) office [8].

Physical treatments of the cervical spine, provided by musculoskeletal physiotherapists can be considered as a treatment option in headache sufferers. The effects of musculoskeletal physiotherapy for various headache types are reported both in RCT's and systematic reviews [9-16]. The combination of mobilisations and low-load exercises focussing on the cranio-cervical flexion is of particular interest nowadays [9,13]. The conclusions of systematic reviews are not firm due to methodological limitations of the selected studies, but there are indications that musculoskeletal physiotherapy directed to the cervical spine can be beneficial for some headache patients [11,15]. Reductions in headache frequency, intensity and duration of headache attacks have been reported [9,13]. Dowson et al. recommend physical therapy (muscle relaxing and mobilising exercises) for those patients who report neck stiffness [17,18]. The neck-headache relationship is however not always causal: neck pain experienced by migraine patients for example can be a result of sensitization [19]. The co-existence of headache and neck pain and/or the presence of neck stiffness might therefore not be a sufficient indication to prescribe physical treatment of the cervical spine.

These therapeutic uncertainties contribute to patients' treatment dissatisfaction. Relatively high percentages of headache sufferers are not satisfied with the headache care they receive. Harpole and co-workers investigated the headache burden and patient satisfaction with existing management in primary care, using patient-administered surveys. Of the 385 responders, who all contacted a GP because of their headache, 48 % reported problems with headache management and 17 % were dissatisfied with the headache care. Patients with a high headache-related impairment reported more problems with their headache management [20]. Walling et al. found that 26 % were dissatisfied in their sample of 447 migraine patients [21].

The prevalence and burden of headache, the dissatisfaction percentages and the diversity in headache treatments, call for a refinement of headache management.

The identification prior to the start of a treatment, of patients whom might react properly to the treatment, is necessary to reduce the risk of a negative outcome. For this purpose, patient characteristics which predict the treatment outcome (prognostic characteristics) need to be determined.

Prognostic factors are multifactorial. Jull and Stanton analysed the results of 152 CErvicogenic Headache (CEH) patients who participated in one of the three active treatment groups in a headache trial [9]. The prognostic value of socio-demographic factors, headache features, physical impairments of the cervical spine, neck pain and disability and patients' perceptions of influences on their headaches (locus of control) was investigated. They were unable to identify a systematic pattern of prognostic factors. Only the presence of light-headedness appeared to be a clinically relevant predictor of a bad outcome. Of the physical tests only joint pain on palpation had a prognostic value [22]. Of their tests only this palpation could be used for prognostic uses.

Our study has a double aim. Our primary aim is to analyse the prognostic value of a series of physical tests. Our secondary aim is to compare two currently applied treatment strategies, being the usual care (UC) administered by a medical doctor following a stepped guideline [7], and the UC plus a musculoskeletal physiotherapy treatment protocol (UCMT), described by Jull et al [9].

Our research questions are: first, can we identify prognostic patient characteristics, and second, what is the additional value of a musculoskeletal physiotherapy approach in the treatment of headache disorders?

## Methods/design

### Study design

A randomised clinical trial with blinded assessment and unblinded treatment and with a follow-up period of 12 months was developed. The research protocol was approved by the Medical Ethics Committees of the University Hospital of the Vrije Universiteit Brussel (UZ Brussel) and of the University Hospital of Antwerp (UZA).

### Patients selection

Using a multicenter setup, patients will be recruited at GPs offices, from outpatient clinics of the neurology department of the academic hospitals UZ Brussel and UZA and via advertisements.

All participating medical doctors (GP's and neurologists) were contacted and personally informed about the study protocol. Additional information is provided on an informative website [23].

The advertisements contain a weblink to an informative recruitment website [24]. On this site detailed information is provided, followed by an online eligibility screenings procedure.

Different recruitment strategies can result in a heterogenous study population. This will not necessarily affect treatment outcome [25]. Subgroups will be compared at baseline. In case differences are found these will be taken into account in the statistical analysis (see section 'Analyses').

### In- and exclusion criteria

Dutch speaking patients with a combination of recurrent headache and neck pain since minimum two months and at least twice a month with an active help-request (who consider to undergo treatment) are recruited. They have to be at least 18 years old and be willing to participate. Subjects are excluded in case of cluster headache or trigeminal neuralgia. To avoid false positive tests with the quantitative sensory tests (see description of measurements), patients with peripheral neuropathies and co-morbidity of chronic musculoskeletal pain will be excluded. Because of the neck mobility tests, people with rheumatoid arthritis, Down syndrome and/or a history of neck surgery will be excluded. The presence of red flags for headache (warning signs for serious causes of the headache) is an extra exclusion criterion. Pregnant women are also excluded, as pregnancy influences the frequency and intensity of headaches with migraine properties.

To avoid biased patients (with treatment preferences), we excluded patients who received physiotherapy treatment for their headaches during the last 12 months or patients whose prescribed medication was changed during the last two months.

The included headache types are migraine, tension-type headache and CEH. For migraine and tension-type headache the IHS criteria are used [26], for CEH the criteria of the Cervicogenic Headache International Study Group (CHISG) [27].

For the patients recruited via internet sites and advertisements, an additional exclusion criteria is set: a HIT-6 score of at least 56 points. From this level, the HIT-6 scoring advises the patient to contact his/her GP in order to start a treatment [28].

All subjects sign a written informed consent.

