##### ■ The Headache Impact Test (HIT-6) [32]

The HIT-6 is a short questionnaire, consisting of 6 items: pain intensity, social functioning, role functioning, vitality, cognitive functioning and psychological distress. It has a recall period of four weeks. Scores vary between 36 and 78. Higher scores correspond with a higher headache burden.

The six items are derived from a total pool of 89 items, 54 items from the computer based HIT pool and 35 items that were proposed by headache experts [32]. Its psychometric properties have been investigated extensively [32,33]. Reliability analyses (internal consistency, alternate forms, test-retest) are good to excellent (scores ranging from 0.78 to 0.90). Construct validity has been investigated using the SF-8 as criterion, and negative correlations were found. The HIT-6 is able to differentiate between mild, moderate and severe headache forms. Pain, role functioning and psychological distress are the most differentiating items. A difference of three points is believed to be clinically important (responsiveness). These results were generated in a general population [32], and were recently confirmed in a population of recent headache sufferers recruited in a headache centre [33].

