### Statistical analyses, power and sample size calculation

The prognostic capacity of the initial series of tests (physical examination of the cervical spine and QST) will be calculated by means of a logistic regression analysis, comparing the results of the responders with those of the non-responders. Instead of starting with a full regression model, two known prognostic factors, derived from the study from Jull and Stanton [8] will be included in the analysis a priori. Those two factors are 'light-headedness' and 'joint pain on palpation'. Consequently a backwards stepwise selection will be used, including the two known factors in the smaller models. Differences at baseline between the two treatment groups will be included in the regression models as potential prognostic factors. The plausibility of the signs will be considered to check the logical contribution of each factor in the model. The power of the obtained models will be analysed via the area under the ROC-curve.

Group differences and effect sizes can be calculated for headache intensity and frequency, medication intake, HIT-6 scores and absenteeism. The number of responders and non-responders in both groups will be compared. GPE is a dichotomous variable. Sample size calculations with a significance level of p < 0.05, an event rate of 0.50 in the usual care group and of 0.70 in the usual care plus musculoskeletal physiotherapy group a power of 80% and an equal amount of subjects in both treatment groups result in a sample size of 93 subjects in each treatment group. This results in a total of 186 subjects.

The results of all subjects will be analysed, regardless of their treatment adherence (intention-to-treat analysis).

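### The HIT-6 cut-off for internet and advertisement recruits is labelled an exclusion at 56 or more, which contradicts its own rationale; it should read as a minimum entry score

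*Protocol article*

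**What the plan says.** The section In- and exclusion criteria adds one rule for a single recruitment route. It begins "For the patients recruited via internet sites and advertisements" and continues "an additional exclusion criteria is set: a HIT-6 score of at least 56 points". The next sentence explains the cut-off: "From this level, the HIT-6 scoring advises the patient to contact his/her GP in order to start a treatment".

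The section on the HIT-6 gives the range, "Scores vary between 36 and 78", and the direction, "Higher scores correspond with a higher headache burden".

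The general entry rule, at the start of In- and exclusion criteria, is that patients "with an active help-request (who consider to undergo treatment) are recruited".

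No other section restates the HIT-6 rule in either direction. No HIT-6 limit is given for patients who come through GP offices or the neurology outpatient clinics. Under Patients selection, the article says that people who respond to advertisements go through an eligibility screen on a website. It does not describe the logic of that screen.

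**The concern.** An eligibility rule is applied as it is written, and this one is written the opposite way from its justification. The label makes 56 a ceiling; the justification only makes sense if 56 is a floor. The two readings select populations that do not overlap.

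The route matters to the trial. According to the Discussion, a pilot limited to first-line recruitment brought in 15 referred patients, and both second-line and advertisement recruitment were then added to reach the required number. If the online screen followed the literal wording, a route opened to fill the sample would supply only lower-burden patients, and no clinician need be involved at that step to notice. Recruitment route would then be tied to headache burden. The primary aim is prognostic, so a population selected in the wrong direction would affect who the prognostic findings describe. HIT-6 is also one of the two primary outcome measures.

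**Working it through.** **Step 1. The two readings on the stated scale.** Inputs: range 36 to 78, higher is worse (HIT-6 section); cut-off 56 (In- and exclusion criteria).

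| Reading | Admitted by advertisement route | Rejected |
|---|---|---|
| As written: 56 or more excludes | 36 to 55 | 56 to 78 |
| As the rationale implies: 56 or more required | 56 to 78 | 36 to 55 |

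The admitted sets are complements, so no patient is eligible under both readings.

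**Step 2. Which reading do the other statements support?**

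- *Rationale sentence.* The score at which a patient is told to see a GP about treatment is a natural point at which to let patients into a treatment trial. It gives no reason to keep them out.
- *Help-seeking requirement.* The trial wants people who are considering treatment. Excluding those whom the score directs towards treatment works against this.
- *Could it be a safeguard that sends high scorers to GP care?* This is implausible. Both arms include usual care by the GP (Interventions), and the Discussion states that no group receives physiotherapy alone.
- *Restriction to one route.* These patients did not come through a doctor. A minimum burden is a sensible stand-in for a consultation. No purpose is stated for a maximum burden.

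All four point to a minimum score of 56. Only the word labelling the criterion points the other way.

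**Step 3. Does any stated figure depend on the direction?** The plan's figure is 93 per group, 186 in total. Inputs (Statistical analyses, power and sample size calculation): "Sample size calculations with a significance level of p < 0.05"; "an event rate of 0.50 in the usual care group"; 0.70 in the other group; 80% power; equal groups. Sidedness is not stated; two-sided is assumed.

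n = [z(0.975) × √(2 × p̄ × (1 − p̄)) + z(0.80) × √(p1(1 − p1) + p2(1 − p2))]² / (p1 − p2)²

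with p̄ = (0.50 + 0.70)/2 = 0.60:

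- 2 × 0.60 × 0.40 = 0.48, square root 0.6928; × 1.960 = 1.358
- 0.25 + 0.21 = 0.46, square root 0.6782; × 0.8416 = 0.571
- (1.358 + 0.571)² / 0.04 = 3.72 / 0.04 = 93

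This reproduces 93 per group, 2 × 93 = 186. HIT-6 does not enter the calculation, so the figure is the same under either reading.

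**Step 4. Room to improve under the literal reading.** From 55 down to the minimum of 36 is 55 − 36 = 19 points. The HIT-6 section takes three points as clinically important, and 19/3 is about 6.3. A patient near 36 would have almost no room, but the article gives no distribution of scores within 36 to 55.

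**The case against.** The strongest reply is that this is a wording slip that most readers would correct for themselves: the explanation follows in the very next sentence, and nothing shows that anyone chose to exclude high-burden patients. That stands as an account of the cause, and the point is accordingly an inconsistency of wording rather than a design decision. It does not remove the need to correct an operative eligibility threshold.

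Several stronger readings are tempting, but the documents do not support them.

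- *A reader might infer that the wrong patients were screened in.* The article mentions the online screen without its logic, so the direction actually used is unknown.
- *A reader might infer that HIT-6 would have little room to improve.* Up to 19 points remain against a three-point important difference, and no score distribution is given, so a floor effect is not shown. The other primary outcome, GPE, which carries the sample size, is not capped by the HIT-6 cut-off.
- *A reader might infer that most of the 186 patients are affected.* No share by route is given, and neurology recruitment was added alongside advertisements.
- *A reader might infer that the treatment comparison is biased.* Patients are randomised after baseline testing whatever their route, so a milder route would not in itself favour either arm.

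The plan also foresees differences between routes. Patients selection provides for comparing recruitment subgroups at baseline and allowing for differences in the analysis, and the Discussion adds a check before pooling. These steps would reveal a severity difference and partly handle it. They would not bring back patients turned away in error.

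**Conclusion.** The criterion is wrong as written and needs correcting. It contradicts the sentence that justifies it, the direction of the scale and the help-seeking requirement, and nothing elsewhere in the article puts it right.

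The size of the consequence is conditional. If the screen was coded literally, the advertisement route would admit only 36 to 55 and lose the whole of 56 to 78, while the other two routes are unrestricted. If it was coded as the rationale implies, the only fault is in the text. The share of patients coming by this route is unknown, so the effect on the full sample cannot be calculated from the article. No planned figure changes.

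This rests on one judgement: that the rationale sentence states the intention and the label is the mistake. The four strands in the working support that, but only the sponsor can confirm it.

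**What to change.** Reconcile the criterion with its rationale by restating it as an inclusion criterion for this route, for example: patients recruited via the internet or advertisements must score at least 56 on the HIT-6 at screening; those scoring below 56 are not eligible.

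Then confirm that the online eligibility screen is coded in that direction. Only if it was not, review those already screened by this route, both admitted and rejected, and report how many were affected.

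The restated rule still sets a limit for one route and not for the others, so the planned baseline comparison of recruitment subgroups should stay.

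The cost is one corrected sentence and one check of the screen's logic. Sample size, outcomes and planned analyses stay as they are.

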### Baseline measurements

Baseline measurements consist of two parts: the completion of questionnaires and physical tests. All baseline measurements are performed by a blinded examiner/rater, as subjects are allocated at random after the baseline measurements (see below: Randomization).

#### A. Questionnaires

All questionnaires can be completed online using PHP-surveyor [29]. In case a participant does not have the opportunity to fill in the questionnaires online, a paper version including an addressed and stamped envelope is provided. The rater is blinded: the online version is completed by the participants themselves, the paper versions are inserted in the computer software by an independent, blinded rater.

##### ■ Headache Diagnosis Questionnaire

This questionnaire was developed to screen for CEH [30]. It consists of 56 questions in total: 34 concerning headache, 15 concerning neck pain and 7 concerning shoulder pain. It registers headache-associated features in a systematic way. Additionally it creates an inventory of pain intensity (Visual Analogue Scale, VAS) of headache, neck pain and shoulder pain (average pain intensity over the last three months and at the moment of fulfilment of the questionnaire), frequency and duration of the headache history. It was developed as a CEH questionnaire and additional questions screening for migraine and tension-type headache characteristics were added. The questionnaire will be validated throughout the trial [30,31].

##### ■ The Headache Impact Test (HIT-6) [32]

The HIT-6 is a short questionnaire, consisting of 6 items: pain intensity, social functioning, role functioning, vitality, cognitive functioning and psychological distress. It has a recall period of four weeks. Scores vary between 36 and 78. Higher scores correspond with a higher headache burden.

The six items are derived from a total pool of 89 items, 54 items from the computer based HIT pool and 35 items that were proposed by headache experts [32]. Its psychometric properties have been investigated extensively [32,33]. Reliability analyses (internal consistency, alternate forms, test-retest) are good to excellent (scores ranging from 0.78 to 0.90). Construct validity has been investigated using the SF-8 as criterion, and negative correlations were found. The HIT-6 is able to differentiate between mild, moderate and severe headache forms. Pain, role functioning and psychological distress are the most differentiating items. A difference of three points is believed to be clinically important (responsiveness). These results were generated in a general population [32], and were recently confirmed in a population of recent headache sufferers recruited in a headache centre [33].

##### ■ Headache Inventory List

This questionnaire is used to register the frequency and intensity of the headache, medication use (both over-the-counter and prescription), headache-related professional care and absenteeism. A similar patient administered questionnaire has been used by Peters et al. [34].

Pain intensity is registered on a VAS for pain at the moment of completion of the questionnaire and for the average pain of the last 4 weeks. Medication intake is monitored, precautionary and treatment medication, both on prescription or over-the-counter.

Headache-related professional care is monitored providing a list of health-care workers who might be contacted by a headache patient (e.g. pharmacist, nurse, and psychologist). Patients have to mark those health-care workers they contacted as well as the frequency of the visits. This registration will allow the analysis of additional therapies that might interfere with the treatment protocol of the study.

Sick leave is scored by the number of absence days.

For all questionnaires a recall period of four weeks is chosen, in correspondence with the recall period of the HIT-6. At baseline and at the last administration of the questionnaires (follow-up at 52 weeks) the absenteeism of the past 12 months is monitored.

